### Inclusion and exclusion criteria

Patients presenting to the GP with any new-onset chest pain or pressure (ventral, dorsal and/or lateral), any left or right upper arm pain or any pain in the epigastric, neck or jaw region, at time of presentation not lasting for more than 24 hours, that is considered to be of possible cardiac origin by the GP will be included. Patients presenting burning sensation on the chest not typical for gastric reflux or anxiety with referral to the chest region are also eligible.

Patients presenting other, less specific complaints possibly matching ACS (dyspnoea, nausea, fatigue, etc.) will only be included if at least one of the above mentioned complaints of pain is co-presenting. Patients will be excluded if an obvious emergency is present (haemodynamic instability, otherwise severely ill patient, etc.). Patients will be excluded if symptoms are present for more than 24 hours, if written informed consent is refused during presentation or withdrawn afterwards, if a traumatic cause is present, if complaints are presented that can be regarded as a recurrence of earlier complaints with clear diagnosis (hyperventilation, stable angina) or in case of death of unidentified cause.

### Data collection

Eligible patients will be evaluated by the GP using the following work up schedule:The GP asks written informed consent using a short version of the consent document in the Netherlands or oral informed consent in Belgium.The GP uses the standardised case report form (CRF-HA) for documentation of history and physical examination. If available and if considered as indicated by the GP, an electrocardiogram (ECG) is performed and documented by the GP.The GP is instructed to fill out the presumptive diagnosis together with the decision whether or not to refer to a cardiologist, *before* performing the H-FABP test.The GP obtains one drop of blood from the patient’s finger and starts the PoC H-FABP test. While the test is running, the GP replaces the test in its cardboard package.At this moment, the GP should wait for no less and no longer than 5 minutes before taking the device out of the package again and reading the result. If the GP is still working on point 1–3 as mentioned above in the 5 minutes waiting time, he cannot be influenced by discolouration of the test.Five minutes after starting the test the result is read. The result has to be added to the CRF-HA directly.

By filling out the presumptive diagnosis together with the decision whether or not to refer to a cardiologist on the CRF-HA before reading the result of the PoC H-FABP-test, the regular decision by the GP whether or not to refer to a cardiologist, which is not influenced by the test result, will be formally recorded. Thus, we will be able to compare this regular care with an algorithm using standardised signs and symptoms with PoC H-FABP-testing. This procedure is seen as the next-best option after complete blinding participating GPs for the test result, which is impossible to realise as test results must be read at the point of care within 5 minutes.

GPs will be instructed to base their referral decisions on the current guidelines on ACS, as is common in the Netherlands and Belgium [43]. Participating GPs will be informed that the PoC H-FABP test is currently under study and that the test results should not influence their decision to refer. Only in the few cases that a PoC H-FABP test is positive after an initial decision not to refer, referral policy will be different from usual care since in that rare occasion, the GP is advised to refer. By following the registration work up as mentioned above, we can still conclude that principally, a referral wouldn’t have been made.

Patients that are not referred to secondary care will be instructed and facilitated to have a venous blood sample drawn within the interval between three hours to three days after onset of complaints. Test results will be primarily used to exclude AMI in non-referred patients based on hsTn analysis. However, the GP is instructed to take notice of the result. If the troponin value is elevated, referral to a cardiologist must take place. Furthermore, renal function, based on creatinine and glomerular filtration rate using MDRD-formulas, will be determined. Collected samples will be preserved for a maximum of 15 years for possible future analysis when relevant.

### Final diagnosis

The participating GP will send the CRF-HA (and ECG, if present) to the research team. The research team will contact the GP and, if referral has taken place and if necessary, the hospital, 30 days after inclusion to collect all relevant patient data. Final diagnosis will be established by an expert panel of one independent GP and one independent cardiologist, based on the outcome definitions. If agreement is not reached within the panel, extension will automatically take place to a panel of two cardiologists and two GPs. The expert panel will be blinded to the PoC H-FABP test performed at initial presentation, but will be given access to all other data. This kind of delayed-type reference standard using an expert panel is considered a reasonable alternative, especially in a low-prevalence setting if the definite reference standard (for example, serial troponin measurements or coronary angiography) is reasonably unavailable for reasons of patient risk, cost, etc. [44]. In cases where final diagnosis of our expert panel appears to be different from the clinical diagnosis made by the treating clinicians, we will follow the diagnosis made by our expert panel.

The definitions of cardiac ischaemic situations – ‘stable angina’ (SA), ‘unstable angina’ (UA), ‘acute myocardial infarction’ (AMI) and ‘heart-related sudden death’ – will be standardised for this study based on current literature and have been settled during a panel discussion with two cardiologists, one GP, an ethicist and two researchers before the trial started. SA will be defined as angina pectoris occurring in a patient in predictable situations for months, without a recent change in severity or amount of exertion that is needed for angina pectoris to occur, whereas UA will be defined as new or altered chest pain due to ischaemia without myocardial cell damage reaching a level where significant changes in myocardial damage-markers can be measured [45,46]. AMI will be defined according to the third universal definition of AMI [27]. This definition is mainly based on the combination of clinical evidence and a rise or fall in biomarker values, preferably hsTn. Exact cut-off values for hsTn will depend on the 99th percentile as is widely accepted. Further judgement on whether STEMI (*ST-segment elevation myocardial infarction*) or NSTEMI (*non-ST-segment elevation (non-Q wave) myocardial infarction*) has occurred will depend on the presence of ST-elevations on the ECG.

The classification ‘none of these’ will refer to complaints that are caused by other than cardiac diseases, or by cardiac, non-ischaemic diseases. Those conditions can be described by ‘atypical thoracic complaints’ or, when available, by the clinical diagnosis (e.g. ‘gastric reflux’ , ‘pericarditis’ , etc.). Acute death of identified cause will refer to any case of death occurring in a patient that meets the inclusion criteria for the study and dies after diagnostic evaluation has reached a point where cause of death can reasonably be determined, or death occurring in a patient before evaluation is done but where post-mortem research is performed to identify cause of death. In all other cases of acute death, the outcome will be defined as acute death of unidentified cause.

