### Primary and secondary outcome

The most important feature of the algorithm of signs and symptoms combined with PoC H-FABP testing will be to adequately categorise all patients as either positive or negative for ACS. The ability of the algorithm to rule in UA in the ACS group is important, since UA is a condition that does not give a rise in biomarkers and diagnosis depends exclusively on signs and symptoms.

Primary outcome: using multivariate analysis of our data, signs and symptoms that have diagnostic value in an algorithm to predict or exclude ACS and AMI will be identified. The primary outcome measures of the study will be *s*ensitivity, specificity, positive and negative predictive value of an algorithm of those relevant signs and symptoms combined with PoC H-FABP testing for ACS and AMI, in patients with thoracic complaints of new onset in general practice. To determine influence of sex, age, duration of the complaints, and kidney function on clinical performance of H-FABP-testing, subgroup analyses within our study population will be performed [47,48].

Secondary outcome: an economic evaluation by means of an incremental cost-effectiveness ratio (ICER) will be performed. This evaluation will be performed by determination of the ratio between the difference in medical costs and the difference in benefits between the two strategies that are observed in this study, being the usual reference policy of the GP and the reference policy that could be created using a determined algorithm consisting of a clinical score and PoC H-FABP-testing. The benefits will be described as reduction in number of referred patients versus missed diagnoses if the algorithm is used.

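### Giving the expert panel all data except the H-FABP result lets it see the comparator and, in some patients, infer the test, mainly at the expense of unstable angina labels

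*Protocol article*

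**What the plan says.** All references are to the protocol article.

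- **Final diagnosis.** The reference standard is a panel diagnosis: "The expert panel will be blinded to the PoC H-FABP test performed at initial presentation, but will be given access to all other data". The case report form (CRF-HA) goes to the research team, which contacts the GP, and the hospital where needed, 30 days after inclusion.
- **Data collection, before the test.** The GP has to "fill out the presumptive diagnosis together with the decision whether or not to refer to a cardiologist" ahead of the finger prick. The test result then goes on the same form: "The result has to be added to the CRF-HA directly".
- **Data collection, after the test.** GPs are told that the result should not influence referral, with one exception: "Only in the few cases that a PoC H-FABP test is positive after an initial decision not to refer" does referral depart from usual care, and then "the GP is advised to refer". Patients who are not referred have a venous troponin, which opens a second route: "If the troponin value is elevated, referral to a cardiologist must take place".
- **Primary and secondary outcome.** On unstable angina (UA) the article says that "UA is a condition that does not give a rise in biomarkers and diagnosis depends exclusively on signs and symptoms".

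The article does not say that the pre-test decision, the presumptive diagnosis or the referral status is withheld from the panel.

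**The concern.** Two kinds of dependence are possible.

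**On the index test.** If a file shows both the decision made before the test and what then happened, the pair carries information on the hidden result. A panel member who suspects a positive H-FABP may lean towards ACS in a borderline case. This matters most for UA, where no biomarker settles the question and panel judgement decides the label.

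**On the comparator.** The algorithm is to be compared with the GP's usual decision. A panel that reads that decision and the presumptive diagnosis may be drawn towards them, which would favour usual care. This needs no inference about H-FABP and could touch any file that contains those entries.

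The two influences need not act in the same direction, so the net bias is unknown in sign and size.

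**Working it through.** **1. The plan's own figure.** Sample size and power calculation uses 600 patients and 22% ACS, hence 132 with and 468 without ACS, with sensitivity 85% and specificity 80%. True positives are 132 × 0.85 = 112.2 and false negatives 19.8; true negatives are 468 × 0.80 = 374.4 and false positives 93.6. PPV = 112.2 / 205.8 = 54.5% and NPV = 374.4 / 394.2 = 95.0%. Wald intervals on rounded counts are 47.6–61.2% and 92.8–97.1%. These agree with the printed 54% (47–61%) and 95% (93–97%) to about rounding. That calculation is not in dispute; its counts are used in step 5. The article gives no figure for how many test results could be inferred.

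**2. What the pairing shows.**

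| Pre-test decision | What then happened | What it suggests about H-FABP |
|---|---|---|
| Refer | Referred | Nothing |
| Do not refer | Referred, troponin not raised | Positive |
| Do not refer | Referred, troponin raised | Little; the troponin explains the referral |
| Do not refer | Not referred | Negative |

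**3. Size of the initially non-referred group.** Inputs: GP sensitivity 81% and specificity 55% (Background, Daily practice). With prevalence p, share = p × (1 − 0.81) + (1 − p) × 0.55.

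- p = 22% (design value): 0.0418 + 0.4290 = 0.471, about 282 of 600.
- p = 13.5%: 0.501, about 301 of 600. This prevalence is not stated. It follows from the quoted PPV of 22%: odds = (0.22 / 0.78) × (0.45 / 0.81) = 0.157, so p = 0.157 / 1.157.
- p = 1.5% (lower end of the quoted range): 0.0029 + 0.5418 = 0.545, about 327 of 600.

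The share is therefore 47–54%. The article's remark that most such patients are referred fits the lower end.

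**4. Strength of the inference.** Let q be H-FABP positivity in this group and a the share of GPs who follow the advice. Neither is given, so I assume q = 3–20% and a = 50–100%.

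- P(negative | stays non-referred) = (1 − q) / [(1 − q) + q(1 − a)]. At q = 20%, a = 50% this is 0.80 / 0.90 = 0.89. With full adherence it is 1.
- P(positive | switched to referral) is 1 if no other route exists. Suppose instead that 5% of the patients whom the test would not move are referred later for reasons that the panel cannot see. It is then 0.01575 / (0.01575 + 0.0485) = 0.25 at q = 3%, a = 50%, and 0.20 / (0.20 + 0.04) = 0.83 at q = 20%, a = 100%.
- Switched test-positives number 282 × q × a, from 282 × 0.03 × 0.5 = 4 to 282 × 0.20 × 1 = 56. The article says only that they are few.
- Test-negatives in the group number 282 × (1 − q), from 226 to 274.

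**5. Why a few labels can matter.** At the design figures the GP detects 132 × 0.81 = 106.9 cases and misses 25.1, all in the initially non-referred group. As an illustration, assume that five patients in that group who are positive by the algorithm are relabelled from non-ACS to ACS. GP sensitivity becomes 106.9 / 137 = 78.0% (from 81.0%) and algorithm sensitivity 117.2 / 137 = 85.5% (from 85.0%). The gap goes from 4.0 to 7.5 points. This shows leverage only; it does not predict how many labels would move.

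**The case against.** A reader might infer that blinding fails in about half the patients. The documents do not support that. The 47–54% is the group in which the result could be guessed. Most of it would be guessed negative, which was likely anyway, and no masking of forms can hide that a patient stayed at home. The positives that could push a label towards ACS are the few switched patients.

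Nor can a reader treat the inference as certain. Referral is only advised, GPs are also told that the result should not influence them, and a raised troponin is a separate route. The article does not say whether the panel can tell a same-day referral from a later one. Ethical considerations adds that the test can have no clinical consequence for the GP's decision, which sits badly with the advice under Data collection. Those passages must be reconciled, and until then adherence is hard to predict.

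A reader might also infer that all accuracy estimates are equally exposed. AMI rests mainly on biomarker change together with clinical evidence, and non-referred patients have a venous troponin planned. The panel is independent, works to definitions fixed in advance, sees 30-day data and is enlarged on disagreement. Exposure is mainly in UA.

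Two further objections stand only in part. Since the form carries the H-FABP result, it must already be masked or abstracted, and a condensed article may leave file preparation to the full protocol. But the article does state the access rule, and that rule excludes nothing else. It can also be said that wide access is deliberate, and that the panel must see the signs and symptoms that drive both the GP's view and the algorithm. That is so, but it does not require showing the panel the comparator itself.

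**Conclusion.** The point holds in a limited form. As written, the access rule lets the panel see the GP's pre-test diagnosis and decision, and lets it pair that decision with the actual referral. The first makes the reference standard open to influence from the comparator. The second weakens blinding to H-FABP, with real consequence chiefly for the few switched test-positives who might have UA.

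The initially non-referred group is 47% at the design's 22% ACS and 47–54% over the quoted range, given the quoted GP accuracy. The number of switched positives cannot be derived from the article; 4 to 56 is the range under assumed positivity of 3–20% and adherence of 50–100%. Direction and size of the net bias are unknown. This should be corrected, but it does not undermine the design.

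**What to change.** Amend Final diagnosis so that, before a file reaches the panel, the research team masks four items:

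- the pre-test presumptive diagnosis;
- the pre-test referral decision;
- the stated reason for referral;
- any mention of H-FABP in GP or hospital letters.

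Keep signs and symptoms, ECG, troponin values with their timing, hospital findings and the 30-day course. With the decision masked, switched patients can no longer be told by this pairing from the roughly 318 (600 − 282) referred from the outset.

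Add one supportive analysis: accuracy of the algorithm in patients referred by the pre-test decision, whose referral does not depend on the test. It checks the algorithm only. Every patient in that subgroup is positive by the GP's decision, so the comparison with usual care cannot be made there, and the case mix differs from the full cohort.

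The cost is some redaction time on forms that already need masking, and the panel loses the GP's impression. Non-referral will still hint at a negative test, so the report should describe the blinding as improved but not complete. No clinical rule changes.

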### Primary and secondary outcome

The most important feature of the algorithm of signs and symptoms combined with PoC H-FABP testing will be to adequately categorise all patients as either positive or negative for ACS. The ability of the algorithm to rule in UA in the ACS group is important, since UA is a condition that does not give a rise in biomarkers and diagnosis depends exclusively on signs and symptoms.

Primary outcome: using multivariate analysis of our data, signs and symptoms that have diagnostic value in an algorithm to predict or exclude ACS and AMI will be identified. The primary outcome measures of the study will be *s*ensitivity, specificity, positive and negative predictive value of an algorithm of those relevant signs and symptoms combined with PoC H-FABP testing for ACS and AMI, in patients with thoracic complaints of new onset in general practice. To determine influence of sex, age, duration of the complaints, and kidney function on clinical performance of H-FABP-testing, subgroup analyses within our study population will be performed [47,48].

Secondary outcome: an economic evaluation by means of an incremental cost-effectiveness ratio (ICER) will be performed. This evaluation will be performed by determination of the ratio between the difference in medical costs and the difference in benefits between the two strategies that are observed in this study, being the usual reference policy of the GP and the reference policy that could be created using a determined algorithm consisting of a clinical score and PoC H-FABP-testing. The benefits will be described as reduction in number of referred patients versus missed diagnoses if the algorithm is used.

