### Study design and objectives

This current study is a derivation study to identify signs and symptoms that, combined with point of care heart-type fatty acid-binding protein (PoC H-FABP) testing, can be part of an algorithm to confirm or rule out ACS (meaning AMI and unstable angina (UA)) and AMI alone in a population of patients with complaints possibly due to myocardial ischaemia in general practice. Thus, stage 2 of the 6 major stages in the development and testing of a clinical decision rule as defined by Stiell and Wells will be studied [42]. The diagnostic value of the algorithm will be studied and compared to regular assessment by a GP without PoC H-FABP testing using a delayed type cross-sectional diagnostic model. Both ACS and AMI as a subgroup of ACS will be analysed as final diagnosis. The cost-effectiveness of the test will also be evaluated. The study commenced in November 2013 and will run for two years. External validation of the algorithm derived from this study needs to be performed in future studies.

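### ACS accuracy of the clinical part of the algorithm is partly exposed to incorporation bias, because the panel that assigns unstable angina sees the same signs and symptoms from which the algorithm is derived

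*Protocol article*

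**What the plan says.** All places are in the Protocol article.

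- **Target.** Study design and objectives names the conditions as "ACS (meaning AMI and unstable angina (UA)) and AMI alone". Both are primary targets.
- **Basis of UA.** Primary and secondary outcome says that "UA is a condition that does not give a rise in biomarkers and diagnosis depends exclusively on signs and symptoms". Final diagnosis gives the working definition: "UA will be defined as new or altered chest pain due to ischaemia without myocardial cell damage" that reaches a measurable marker change.
- **Index test.** The accuracy measures are for "an algorithm of those relevant signs and symptoms combined with PoC H-FABP testing for ACS and AMI".
- **Source of the predictors.** Data collection: "The GP uses the standardised case report form (CRF-HA) for documentation of history and physical examination". The GP's presumptive diagnosis and referral decision go on the same form.
- **Route of the form.** Final diagnosis: "The participating GP will send the CRF-HA (and ECG, if present) to the research team".
- **Panel blinding.** Final diagnosis: "The expert panel will be blinded to the PoC H-FABP test performed at initial presentation, but will be given access to all other data". The same section says that GP data and, where needed, hospital data are collected 30 days after inclusion, and it defends the delayed panel as a reasonable reference where a definite standard is unavailable.

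**The concern.** A diagnostic accuracy estimate assumes that the reference diagnosis is made independently of the index test. Here the index test has two parts. H-FABP is protected by the blinding. The clinical part is not, because the panel may use the recorded history and examination when it decides on UA. A symptom that panel members regard as typical can then be found to predict ACS because it contributed to the label. Atypical UA that the panel places in the residual class no longer counts as a miss.

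This matters most for rule-out. Sample size and power calculation expects a worst-case NPV of 95%, equal to the 95% quoted for current clinical judgement, so a modest upward bias could hide a loss. The article does not mention the overlap. Its Discussion names inter-observer reliability as the only criterion of a methodologically correct derivation study that is not met.

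**Working it through.** **Step 1: the passages side by side.** UA is part of ACS. UA gives no marker rise by the plan's own statement, so a normal troponin does not separate UA from a non-cardiac cause. The algorithm uses history and examination items from the case report form. That form goes to the research team, and the panel is denied only the H-FABP result. The article does not list the panel's file item by item, but access to everything else includes these items on any plain reading. The overlap follows.

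**Step 2: what else the panel has.** An ECG if one was made; troponin from the venous sample in non-referred patients; GP and, where needed, hospital data at 30 days. The label is therefore not built from the predictors alone. Non-referred patients have no hospital work-up from an index referral, so the overlap is likely to be largest there.

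**Step 3: the plan's own figures.** Inputs from Sample size and power calculation: N = 600, ACS 22%, sensitivity 85%, specificity 80%.

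- With ACS 600 × 0.22 = 132; without ACS 468.
- TP = 132 × 0.85 = 112.2; FN = 19.8; TN = 468 × 0.80 = 374.4; FP = 93.6.
- PPV = 112.2 / 205.8 = 54.5% (95% Wald interval 47.7-61.3%).
- NPV = 374.4 / 394.2 = 95.0% (92.8-97.1%).

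The stated 54% (47-61%) and 95% (93-97%) reproduce within one percentage point. They carry no allowance for overlap between predictors and reference diagnosis.

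**Step 4: illustration.** Neither of the next two inputs is in the documents; both are assumptions. Let u be the UA share of ACS (20-50%) and d the rise in apparent sensitivity within UA (5-15 points). Hold specificity at 80% and the ACS count at 132, which is a simplification, since relabelling would also move patients between ACS and non-ACS.

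Apparent ACS sensitivity = true sensitivity + u × d. NPV = 374.4 / (374.4 + 132 × (1 − sensitivity)).

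The smallest rise is 0.20 × 5 = 1.0 point and the largest 0.50 × 15 = 7.5 points.

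| True sensitivity | True NPV | Apparent sensitivity | Apparent NPV |
|---|---|---|---|
| 80% | 374.4 / 400.8 = 93.4% | 81.0-87.5% | 93.7-95.8% |
| 85% | 374.4 / 394.2 = 95.0% | 86.0-92.5% | 95.3-97.4% |

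A true 80% appears as 85% or more only when u × d is at least 5 points: for example u = 50% with d = 10 (85.0%, NPV 95.0%), or u = 35% with d = 15 (85.25%, NPV 95.1%). With u = 20% it stays below 85% throughout the assumed range.

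**The case against.** The sentence about UA resting exclusively on signs and symptoms explains why the algorithm must capture UA without a marker; it is not the panel's rule. The panel works from outcome definitions that require a judgement of ischaemia, with ECG, troponin and 30-day data at hand. Infarction alone is also a primary target, and its definition leans mainly on clinical evidence with a biomarker rise or fall. UA is a separate panel class, so sensitivity within UA can be obtained from planned data. The study is presented as a derivation study with validation to follow.

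Much of this stands, and it limits the point. A reader might infer that the UA label and the algorithm are the same information, so that the ACS result is wholly circular. The documents do not support that, because the panel has other evidence. A reader might also attach a large number. Take 90% sensitivity for infarction, 60-80% true and 95% apparent sensitivity for UA, and a UA share of 30-50%. The excess is then 0.30 × 15 = 4.5 to 0.50 × 35 = 17.5 points. Every one of those inputs is from outside the documents, and the 95% assumes near-total circularity, which is the matter in dispute. Nor can one infer that the algorithm's advantage over the GP is inflated: the GP's judgement draws on the same history and examination, so both may be flattered.

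What does not answer the point: H-FABP blinding leaves the clinical component exposed, infarction-only results do not repair the ACS result, and later validation with the same kind of panel would carry the same overlap. An analysis plan cannot separate supported from unsupported UA unless the basis of each diagnosis is recorded.

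**Conclusion.** The point holds in a limited form. Accuracy for ACS is partly exposed to incorporation bias through UA, and the bias in absolute accuracy is probably upward. It concerns the clinical component; the H-FABP component is blinded and infarction alone is much less exposed. The 1.0-7.5 point range is an illustration under assumed UA shares and inflation, not an estimate. It shows that a rule with NPV below the current 95% could, under the less favourable assumptions, appear to meet the target. The direction of bias in the comparison with GP judgement cannot be determined. The design remains usable, but the ACS rule-out result should carry this qualification and the data needed to judge it.

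**What to change.** 1. Add one field to the panel form: for each UA case, whether the diagnosis is supported by evidence beyond the index history and examination (ECG change, hospital testing, or an event by day 30).
2. Report the algorithm's sensitivity separately for infarction and for UA, beside ACS overall, with the UA share.
3. As a sensitivity analysis, repeat the ACS accuracy with unsupported UA first excluded and then counted as non-ACS. Show the results by referral status, because support is more likely to exist in referred patients.
4. Keep ACS as the primary target as planned. State that its rule-out result is subject to incorporation bias unless it is consistent across these analyses and infarction alone. The restricted definition should not become the sole basis of a rule-out claim: referral follows the GP's clinical assessment, so supported UA is itself a selected group.

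Cost: one form field and a few extra analyses; no added patients or procedures. Precision falls. With an assumed UA share of 20-50%, there are 132 × 0.20 = 26 to 132 × 0.50 = 66 UA cases. At 85% sensitivity the 95% half-width is 1.96 × √(0.85 × 0.15 / n), which is about 14 points for 26 cases and 9 for 66, against 6 for all 132. This loss, and the possible selection through referral, should be stated with the results.
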